**Methods/design:**

The PMP will be offered to federally qualified health centers and charity clinics in the Greater Houston area using a non-randomized stepped wedge design. Due to practical constraints of implementing and adopting in the real-world, randomization of start times and blinding will not be used. Any potential confounding or bias will be controlled in the analysis. Outcomes such as appointment adherence, patient referral to diagnostics, time to diagnostic referral, patient referral to treatment, time to treatment referral, and budget impact of the intervention will be assessed. Assessment of constructs from the consolidated framework for implementation research (CFIR) will be assessed during implementation and at the end of the study (sustainment) from each participating clinic. Data will be analyzed using descriptive statistics (chi-square tests) and generalized estimating equations (GEE).

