### Sample size

Sample size for the stepped wedge design is calculated using the formula of Woertman et al. 2013 [32], which corrects a standard sample size calculation for two independent proportions as follows:$$ Nsw= Nu* DEsw $$

where *Nu* equals the uncorrected sample size estimate and *DEsw* is the design effect for the stepped wedge design.$$ DEsw=1+\rho \left(ktn+bn-1\right)*\frac{3\left(1-p\right)}{\left(1+p\right)\left(\frac{1}{2ktn}+bn-1\right)2t\left(k-\frac{1}{k}\right)} $$

where *ρ* equals the intraclass correlation, *k* equals the number of steps, *b* equals the number of baseline measurements, *t* equals the number of intervention measurements, and *n* equals cluster size. The uncorrected sample size for a difference in two independent proportions assuming a baseline no-show rate of 35 % reduced to 28 %, an α of 0.05 and a power of 0.9 equals 924 per group. The average no-show rate and expected reduction in no-shows are based on pilot studies [20, 30]. The intraclass correlation coefficient (ICC), *p*, for mammography screening interventions has been shown to range from 0.0009 to 0.22 in community-based trials with an average ICC of 0.06 based on recent systematic reviews [33, 34]. Estimated sample sizes based on these parameters are summarized in Table 1. Based on the average reported ICC, the required sample size is 388 women. The required number of clusters is calculated as *Nsw/n* resulting in an effective sample size requirement of seven clusters (clinics) [32]. In order to account for potential attrition estimated based on the investigator’s pilot study, the sample size will be increased by 20 % to 466 women across nine clinics.

**Table 1 Tab1:** Estimated sample sizes based on ICC reported values

*Nsw*	*Nu*	*DEsw*	*p* (ICC)
370	1848	0.20	0.006
388	1848	0.21	0.06
370	1848	0.20	0.1
333	1848	0.18	0.22

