### Randomization and allocation

Clinic will be the unit of allocation in this study. Each clinic will be assigned a start date in groups of three (Fig. 1). Randomization of clinic start dates will not be done for practical reasons, including constraints in clinic operations (requirements for when they can or cannot start) and available screening dates (some clinics need additional time to reach the screening minimums required for study participation (*n* = 6)). The research team will assign a start date to each clinic based on these constraints.

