### Outcome measures

The primary outcome measure will be appointment adherence comparing the intervention period to the baseline period in each clinic. Appointment adherence will be considered using the following categories: no-show, not attended-called, late-screened, late-turned away, canceled/re-scheduled, and ineligible. A no-show will be considered a patient who makes no contact with the clinic prior to the appointment and does not attend on the day of mammography screening. A not attended-called is a patient who calls the clinic the day of the screening and asks to cancel or re-schedule (this may occur before or after their designated appointment time). Late-screened is a patient who arrives more than 30-min late for their appointment but is still seen by the mammography provided (e.g., worked in). Late-turned away is a patient who is more than 30-min late for their appointment and is turned away by the provider. A cancel or re-schedule is a patient who calls more than 24 h in advance to cancel or change their appointment date. An ineligible patient is a woman with symptoms who is ineligible to receive a screening mammogram and is turned away for a diagnostic evaluation or a woman who is turned away for incomplete paperwork. These categories are based on an assessment of the mammography providers’ and clinics’ behavior and the ways in which patient appointment outcomes are considered within a clinic system. Secondary measures will include patient referral to diagnostic (following screening) as a binary outcome and amount of time the referral took in days, patient referral to treatment as a binary outcome and the amount of time it took in days, and measures of implementation in each clinic based on the consolidated framework for implementation research (CFIR). A survey made up of scales assessing various CFIR constructs was developed by the Cancer Prevention and Control Research Network (CPCRN); we will use several scales from that survey in this study. These constructs will be measured at baseline (adoption), 8-week post-implementation, and following the end of the trial period (sustainment) [35–37]. Because randomization of start dates is not possible, we will control for potential confounders in the analysis of the data. Control variables may include time to intervention start date in each clinic, clinic size, staffing, and whether or not the clinic had a pre-existing patient navigation program for breast cancer screening, patient demographics, region served, and infrastructure characteristics (e.g., funding) (taken from the Health Resources and Services Administration Uniform Data System (UDS) reports for FQHCs and our economic survey).

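### Start dates follow clinic constraints, but the stated model commits to neither a clinic (or wave) term nor calendar period, so it does not secure the within-clinic comparison the plan claims

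*Protocol article*

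**What the plan says.** **Allocation.** Under Randomization and allocation, clinics start in groups of three, and the dates depend on clinic operations and on how long a clinic needs to reach the required screening minimum: "The research team will assign a start date to each clinic based on these constraints".

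**Promise.** The abstract (Methods/design) states: "Any potential confounding or bias will be controlled in the analysis". Trial design says each clinic acts as its own control. Outcome measures defines the contrast accordingly: "The primary outcome measure will be appointment adherence comparing the intervention period to the baseline period in each clinic". Blinding says the analysis will be pre-specified.

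**Stated adjustment.** Outcome measures says "Because randomization of start dates is not possible, we will control for potential confounders in the analysis of the data" and continues: "Control variables may include time to intervention start date in each clinic, clinic size, staffing", followed by prior navigation, patient demographics, region and infrastructure. Statistical methods names GEE as the model and gives time, clinic size, staffing and prior navigation as examples of confounders. It names no working correlation. For the adherence sub-categories it plans chi-square tests of control against intervention, with no adjustment mentioned.

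**The concern.** Start order is tied to clinic characteristics such as screening volume and readiness. If early and late clinics differ in their underlying no-show rate, any estimate that compares clinics with one another absorbs part of that difference. A population-averaged GEE uses both within-clinic and between-clinic information unless a clinic or wave term removes the latter. Naming the contrast as within-clinic does not change what the model estimates.

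Calendar time is a separate problem. Intervention periods fall later than baseline periods by design, so a regional trend in attendance looks like an effect unless calendar period is in the model. Time to intervention start is a fixed attribute of a clinic, not calendar time. It cannot do this job.

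The two terms are needed together. Period alone does not deal with early-late differences and, as shown below, lets more of them through.

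**Working it through.** **The plan's own figures.** Sample size uses "assuming a baseline no-show rate of 35 % reduced to 28" per cent and "an α of 0.05 and a power of 0.9 equals 924 per group". With pooled variance, two-sided:

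n = [1.960·√(2·0.315·0.685) + 1.282·√(0.35·0.65 + 0.28·0.72)]² / 0.07² = (1.288 + 0.839)² / 0.0049 ≈ 923.3, so 924 per group. Then 1848 × 0.21 = 388, and 388 × 1.2 = 466. These reproduce. The yardstick is therefore a 7-point effect.

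**Inputs.** From the article: 9 clinics in three groups; 466 women planned and about 2200 expected (Trial status); the ICC, "with an average ICC of 0.06 based on recent systematic reviews"; and 0.006, the lowest ICC in Table 1. Assumed, because Fig. 1 is not shown: 4 equal periods, equal cells, one wave crossing over at each of periods 2, 3 and 4, and a linear probability scale. The early-late gap G (wave 1 minus wave 3) is not in the article.

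**Sums of squares of the exposure X, per one clinic in each wave (12 cells).** Exposed fractions are 3/4, 2/4 and 1/4.
- Between clinics: 4 × (0.25² + 0 + 0.25²) = 0.5
- Within clinics: 0.75 + 1 + 0.75 = 2.5
- Total after removing period: 6/9 + 6/9 = 4/3, so within clinics after period: 4/3 − 1/2 = 5/6
- Cross-product of a wave difference with X: 4 × 0.25 × G = G, all of it between clinics (the middle wave cancels)

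**Weight on between-clinic information.** With n women per cell and exchangeable ICC ρ:

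λ = [(1−ρ)/n] / [(1−ρ)/n + 4ρ]; independence corresponds to λ = 1.

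**Share of the gap that enters the effect.**
- Period in the model, no clinic or wave term: λ / (5/6 + λ/2)
- Neither term: λ / (2.5 + λ/2)
- Clinic plus period, wave plus period, or linear time-to-start plus period: 0, because the between-clinic part is removed

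| Working correlation | Women (n per cell) | λ | Neither term | Period only |
|---|---|---|---|---|
| Independence | any | 1 | 0.33 | 0.75 |
| Exchangeable, 0.006 | 466 (12.9) | 0.76 | 0.26 | 0.63 |
| Exchangeable, 0.006 | 2200 (61.1) | 0.40 | 0.15 | 0.39 |
| Exchangeable, 0.06 | 466 (12.9) | 0.23 | 0.09 | 0.24 |
| Exchangeable, 0.06 | 2200 (61.1) | 0.06 | 0.02 | 0.07 |

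With period only, an assumed 10-point gap gives, in the same row order, 7.5, 6.3, 3.9, 2.4 and 0.7 points of spurious effect. Assumed gaps of 5 and 15 points give 3.8 and 11.3 points under independence.

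**Omitting calendar period.** For a change of 1 point per period the cross-product with X is 1.5 + 2 + 1.5 = 5, all within clinics. The spurious effect is 5 / (2.5 + λ/2): 1.67 points at λ = 1, 1.98 at λ = 0.06, and 5/2.5 = 2.0 with clinic effects but no period. With period in the model it is 0.

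**Price of clinic effects.** The standard-error ratio against the exchangeable model with period is √[(5/6 + λ/2)/(5/6)] = √(1 + 0.6λ). This gives 1.02 (ICC 0.06) and 1.11 (ICC 0.006) at 2200 women, and 1.07 and 1.21 at 466.

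**The case against.** The strongest reply is that this is a journal article, that its covariate lists are openly illustrative, and that clinic terms, period terms and working correlation belong in an analysis plan that is not shown. Part of this stands. Nothing says these terms will be left out, time is the first confounder that Statistical methods names, and missing detail alone would not be a point. But the article does more than stay silent. It describes an adjustment strategy and says it will control confounding and deliver a within-clinic comparison. The strategy as written does not guarantee either.

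Three stronger readings are tempting, and the documents do not support them.

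- *That the plan will produce a false effect as large as the planned one.* This needs an independence working correlation, which the article never states; it chooses GEE because observations within a clinic are correlated. With exchangeable correlation, ICC 0.06 and 2200 women, leakage is about 7% of the gap. The gap itself is assumed.
- *That clinic fixed effects are the only remedy.* Time to intervention start is already on the Outcome measures list. If always included alongside calendar period, it also gives zero bias in the balanced layout. The difficulty is that the list makes it optional.
- *That simulated false-positive rates measure the confounding.* With nine clusters, uncorrected sandwich errors over-reject anyway. In 500 simulated trials with no gap and no trend, an exchangeable GEE without period rejected in 10%, and the clinic-plus-period model in 11%. Raw rejection rates mix this inflation with bias, so the point rests on the bias figures.

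The covariate list is also not purely clinic-level, since it includes patient demographics.

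**Conclusion.** The point holds as a gap between what the plan claims and what its stated model secures. Non-random start dates make early-late clinic differences plausible, and neither of the two terms that would neutralise those differences and secular trend is a committed part of the model.

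The size depends heavily on unstated choices. With period only, between 7% and 75% of an early-late gap reaches the effect, according to working correlation, ICC and sample size. Without period, each 1-point change per period adds about 1.7 to 2.0 points, against a planned 7. The percentages rest on the assumed balanced layout and linear scale. The article gives neither a gap nor a trend, so no actual bias is shown.

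**What to change.** State the primary model as: outcome on PMP indicator, clinic indicators and categorical calendar period (periods as laid out in Fig. 1), with patient-level covariates. As a minimum alternative to clinic indicators, always include wave indicators or time to start; the zero-bias result for these was checked only in the balanced layout.

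With clinic indicators, drop the time-constant clinic-level covariates. The indicators absorb them, and nine clinics could not support the whole list in any case. Apply the same adjusted model to the adherence sub-categories in place of the unadjusted chi-square tests of control against intervention.

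The change is one of wording; Trial status reports that baseline measures were still being collected. The cost is precision: standard errors about 2% (ICC 0.06) to 11% (ICC 0.006) larger at 2200 women, and about 7% to 21% larger at 466. Two things stay unresolved. Clinic effects do not remove clinic-specific trends, and this fix does not cure small-cluster inflation of sandwich-based tests.

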
### Data collection

Data collection protocols will be standardized across all clinics. In clinics with the capability to collect and report data from their electronic health record (EHR), the research team will seek to adapt the existing system for data collection. In clinics where the EHR is not easily modified or one is not available, data collection will be supported via the use of a customized Redcap database. The database will have a front-facing data entry interface which is user friendly and supports accurate data collection for statistical analysis. The patient navigator (or implementer) in each clinic will be responsible for tracking upcoming patient mammography appointments, reminder phone call attempts, patient consent for the trial, and the EBI screening questions and barriers counseled during the phone call. Appointment attendance, referral to diagnostic mammography, and treatment data will be abstracted from medical records in each clinic. For the budget impact analysis, two surveys will be used to assess the FQHC/clinic resource utilization before and after the implementation of the intervention. We are also collecting patient resource utilization data to understand what parts of patient costs are being subsidized by the FQHCs/clinics and to also ensure availability of cost information from patient perspective in case an economic evaluation from societal perspective is deemed important.

### Statistical methods

Descriptive statistics will be calculated for all primary and secondary measures. Following descriptive analysis, regression modeling will be used to evaluate outcomes while allowing for control of potential confounders (e.g., time, clinic size, staffing, and whether or not the clinic had a pre-existing patient navigation program for breast cancer screening). Due to the correlated nature of the data and repeated observations taken on each clinic, generalized estimating equations (GEE) will be used to model outcomes while allowing us to control for potential confounders [38, 39]. GEE is used to estimate the parameters from a generalized linear model when there is possible correlation between outcomes [38, 39]. GEE is a population averaged model that estimates the average response from a change in a covariate over the population rather than individual [38, 39]. GEE model estimates are less sensitive than generalized linear mixed models to the specification of the variance structure in the data making them a flexible choice [38, 39]. Data on appointment adherence will be analyzed using various sub-groups to evaluate the intervention effect. For example, no-shows and not attended-called may be combined to consider a more stringent definition of a no-show. They will also be analyzed separately. We expect the intervention to have an effect on the no-shows, not attended-called, late-screened, late-turned away and ineligible categories and will evaluate that effect separately. Sub-categories will be compared using chi-square tests to determine differences in outcomes between groups (control and intervention). Data from the CFIR survey will be analyzed using descriptive statistics and in the regression models to evaluate which constructs are related to implementation outcomes. Data analysis will be conducted in Stata (Stata Corp., College Station, TX).

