
### Trial status

The trial has completed enrollment of the first wave of clinics (*n* = 9) and is currently collecting baseline measures at these locations. Baseline measures include appointment adherence outcomes as described above, the clinic and patient resource utilization survey for the budget impact analysis, and CFIR survey. All participating clinics have completed the baseline CFIR survey. Based on the number of mammography screening drives at each clinic, we anticipate enrolling approximately 2200 women into the first wave of the trial.

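### GEE on nine clinics is justified by a many-cluster property; without a small-sample correction the nominal 5% primary test could run at roughly 10% to 20%

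*Protocol article*

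**What the plan says.** The Statistical methods section states that "generalized estimating equations (GEE) will be used to model outcomes while allowing us to control for potential confounders". The reason it gives for preferring GEE to mixed models is that "GEE model estimates are less sensitive than generalized linear mixed models to the specification of the variance structure". Stata is named as the software. The section does not name the type of standard error, the working correlation, the reference distribution or any finite-sample correction.

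The number of clusters comes from other sections. Sample size requires seven clinics and raises this for attrition to "466 women across nine clinics". Randomization and allocation says "Each clinic will be assigned a start date in groups of three", on dates set by the research team rather than at random. Trial status reports nine clinics enrolled and about 2200 women expected.

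Statistical methods plans adjustment for time, clinic size, staffing and any pre-existing navigation program. Outcome measures adds further clinic-level candidates: time to start date, region served and infrastructure.

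**The concern.** The sandwich variance is what keeps GEE tests and intervals valid when the working correlation is wrong. It is justified as the number of clusters grows. With nine clusters it is biased downward and is itself noisy, so comparing the ratio of estimate to standard error with 1.96 rejects too often. More women per clinic do not cure this, because the limit is the number of clinics. The property offered as the reason for GEE is therefore weak in this design, exactly where the primary test would rely on it.

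The false-positive rate and the interval width of the primary effect are at stake. Two features of the plan add weight. Start dates are not randomized, so no randomization-based test is available as a fallback and inference rests on the model. The Blinding section also offers pre-specification of the analysis as the safeguard in place of a blinded analyst.

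**Working it through.** **Inputs.** From the protocol: nine clinics in three groups of three; no-show rate 35% against 28%; α 0.05; power 0.9; average ICC 0.06, with Table 1 running from 0.006 to 0.22; 466 women planned (466/9 ≈ 52 per clinic) and about 2200 expected (2200/9 ≈ 244 per clinic). Assumed: four periods, which gives 52/4 = 13 or 244/4 = 61 women per clinic-period; a binary no-show outcome; a logistic GEE with exchangeable working correlation.

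**The plan's own figure.** The protocol states its uncorrected sample size as "assuming a baseline no-show rate of 35 % reduced to 28 %, an α of 0.05 and a power of 0.9 equals 924 per group". Two-sided with pooled variance: p̄ = 0.315, and n = [1.960·√(2·0.315·0.685) + 1.282·√(0.35·0.65 + 0.28·0.72)]² / 0.07² = (1.2875 + 0.8395)² / 0.0049 ≈ 923.3, rounded up to 924. It reproduces. Also 388 × 1.2 = 465.6, i.e. 466. The protocol gives no type I error for the GEE test other than α.

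**Rough analytic check.** Take the robust standard error as shrunk by √((K−2)/K), with the ratio truly following t on K−2 df. For K = 9, the effective cut-off is 1.96·√(7/9) = 1.729, and P(|t(7)| > 1.729) = 12.8%. Without the shrinkage, P(|t(7)| > 1.96) = 9.1%.

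**Null simulation of the design** (nominal 5%, ICC 0.06 unless stated; first five rows 5000 runs each, last four 2000 each):

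| Setting | Robust SE, normal | Robust SE, t(7) | Mancl-DeRouen, t(7) | Model-based SE, normal |
|---|---|---|---|---|
| 52 per clinic, equal sizes, period terms | 13.5% | 7.9% | 3.5% | 6.1% |
| 244 per clinic, equal sizes, period terms | 13.1% | 7.7% | 3.1% | 5.4% |
| 52 per clinic, equal sizes, no period terms | 9.6% | 5.0% | 3.6% | 4.5% |
| 244 per clinic, equal sizes, no period terms | 10.2% | 5.6% | 3.6% | 4.3% |
| 52 per clinic, unequal sizes, period terms | 14.9% | 9.2% | 3.5% | 6.9% |
| 52 per clinic, period terms, three clinic covariates | 16.7% | 11.1% | 2.1% | 7.9% |
| 244 per clinic, period terms, three clinic covariates | 15.3% | 10.0% | 2.5% | 7.1% |
| 244 per clinic, period terms, cluster autocorrelation 0.8 | 14.8% | 9.2% | 3.4% | 14.1% |
| As above, ICC 0.22 | 14.9% | 9.2% | 2.8% | 30.3% |

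Within the 2000-run set, adding three clinic-level covariates moved the uncorrected robust test from 15.5% to 16.7% (52 per clinic) and from 13.2% to 15.3% (244 per clinic).

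**Ranges over all settings run.**
- Uncorrected robust SE with a normal reference: 9.6% to 17.6%, with mean SE divided by true SD from 0.74 to 0.92.
- Uncorrected robust SE with t(7): 5% to 11%.
- Mancl-DeRouen with t(7): 2% to 5%.
- Model-based SE, exchangeable structure correct: 4% to 9%.
- Model-based SE, correlation decaying between periods: 7% to 35% at ICC 0.06 and 0.22. At ICC 0.006 it stays at 6% to 8%, because there is little correlation to misspecify.

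**Agreement.** Two further null simulations of the same design gave, for the uncorrected robust z test, 13.3% (ICC 0.06, about 2200 women, 1500 runs; mean SE 0.137 against true SD 0.167, ratio 0.82) and 12.6% (ICC 0.06, 61 per clinic-period). The second ranged from 10% to 20% over its settings, and gave 5% to 13% for a model-based SE and about 3% to 4% for Mancl-DeRouen with t(7), with or without three clinic-level covariates.

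**The case against.** The strongest reply is that the faulted test is not in the document. A reader might infer that the protocol has chosen an uncorrected test and that its primary analysis has a 13% error rate. The text does not support that. It names no standard error or reference distribution and neither adopts nor rules out a correction; naming Stata does not settle the matter. Such detail is commonly left to an analysis plan, and none is shown. This stands: the size is conditional, and silence on the correction is not itself an error.

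A second reply is that the quoted sentence speaks of estimates. For point estimates, insensitivity to the working correlation comes from the mean model and does not need the sandwich. That is fair. But the sentence is offered as the reason for choosing the method that will deliver the test and interval, and there the property needs the sandwich and many clusters.

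A third reply is that the standard error could be model-based. That does not rescue the stated rationale. The test then depends on the working correlation being right, which is the sensitivity that GEE was chosen to avoid.

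A fourth is that nine may not be final, since "The trial has completed enrollment of the first wave of clinics". No later number is given and Sample size plans for nine. On the rough formula, 18 clinics would still give about 8% (cut-off 1.96·√(16/18) = 1.848 on t(16)). Attrition to seven would give about 16% (1.96·√(5/7) = 1.656 on t(5)).

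**Conclusion.** The point holds in conditional form. What the document fixes, GEE on nine clinics, is paired with a justification that does not carry over to tests and intervals at that number of clusters. If the robust standard error is left uncorrected and referred to the normal distribution, the nominal 5% primary test would run at roughly 10% to 20%, about 13% centrally. The planned clinic-level covariates push it towards the upper half of that range. These figures rest on four assumed periods, a binary no-show outcome at 35%, an exchangeable working correlation and ICCs from 0.006 to 0.22.

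It would go too far to conclude that GEE is the wrong method here: with a correction it holds its level. It would also go too far to treat 13% as a property of the plan as written. The matter should be settled before analysis, and if an analysis plan already specifies a correction, only the rationale in the protocol needs aligning.

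**What to change.** State for the primary GEE: a small-sample bias-corrected sandwich variance (Mancl-DeRouen, or Kauermann-Carroll), with a t reference on cluster-based degrees of freedom (clinics minus 2, here 7, or Satterthwaite). Both parts are needed, since t(7) with an uncorrected sandwich still gives 5% to 11%. The tabulated results are for Mancl-DeRouen; if Kauermann-Carroll is preferred, check its size on the same design. Name the working correlation, and limit the clinic-level covariates to a short pre-specified list: the protocol mentions about six candidates for nine clinics.

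The cost is one or two sentences and no new data. Intervals widen. With the simulated SE of 0.137 against a true SD of 0.167, and assuming the corrected SE averages the true SD, the half-width on the log-odds scale goes from 1.96 × 0.137 = 0.269 to 2.365 × 0.167 = 0.395, about 1.47 times as wide. That is the honest width rather than a loss caused by the correction. Mancl-DeRouen may be slightly conservative (about 2% with three clinic-level covariates). Because the sample size rests on normal critical values, power should be recalculated for the corrected test.

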### Ethical approval

This study has received approval from the Institutional Review Board at the University of Texas Health Science Center Houston. The protocol number is HSC-SPH-14-0269. Verbal consent will be obtained for patients participating in the EBI reminder phone calls. Written consent will be obtained for economic data collection from patients.

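### Appointment adherence, the primary outcome, is never reduced to one endpoint, and the sample size is calculated for no-shows only

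*Protocol article*

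**What the plan says.** Trial objectives hypothesises that the program improves mammography appointment adherence compared with usual practice. Outcome measures follows this: "The primary outcome measure will be appointment adherence comparing the intervention period to the baseline period in each clinic". It then defines the outcome by a list: "Appointment adherence will be considered using the following categories: no-show, not attended-called, late-screened, late-turned away, canceled/re-scheduled, and ineligible". No category covers a woman who attends on time, and nothing says which categories count as adherent.

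Statistical methods expects effects on no-shows, not attended-called and the "late-screened, late-turned away and ineligible categories and will evaluate that effect separately". That makes five of the six; canceled/re-scheduled is absent and no reason is given. The same section says that "no-shows and not attended-called may be combined to consider a more stringent definition of a no-show", and that the two will also be analysed apart. Sub-categories are to be compared by chi-square tests.

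Sample size uses a single proportion, "assuming a baseline no-show rate of 35 % reduced to 28" per cent. The Abstract's discussion expects fewer no-shows, and Budget impact analysis names adherence and no-show rates side by side as the primary goal. Blinding relies on pre-specification because neither the clinics, the research team nor the analyst can be blinded.

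**The concern.** The hypothesis, the outcome definition, the analysis and the sample size do not refer to the same quantity. The six categories mix absence (no-show, not attended-called, canceled/re-scheduled), attendance (late-screened, a woman "more than 30-min late for their appointment but is still seen by the mammography provided"), late arrival without screening, and ineligibility. Without an assignment rule, two analysts could each follow the article and report different primary results.

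Two things are at stake. First, the proportion used for power can improve without more women being screened as booked, because a no-show is defined by the absence of contact: a woman who cancels in good time leaves the no-show count but is still not screened that day. Second, with several categories evaluated separately and a composite left optional, there is more than one route to a positive primary claim in an unblinded, non-randomised trial whose stated safeguard is pre-specification.

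**Working it through.** **1. Reproduce the planning figure.** Inputs from Sample size: p1 = 0.35, p2 = 0.28, α = 0.05, power 0.9. Sidedness is not stated; two-sided is assumed here.

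n = [z(0.975)·√(2·p̄·q̄) + z(0.90)·√(p1q1 + p2q2)]² / (p1 − p2)², with p̄ = 0.315

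= [1.960 × 0.6569 + 1.2816 × 0.6551]² / 0.07² = 2.127² / 0.0049 ≈ 923.3, so **924 per group**, 1848 in total.

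This matches the article. A one-sided test would give 753. Then 1848 × 0.21 = 388.1 and 388 × 1.2 = 465.6, matching 388 and 466. Every sample size that follows from 924 therefore rests on the no-show proportion; no rate for adherence or attendance is used anywhere.

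**2. Compare the outcome across sections.**

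| Section | Quantity |
|---|---|
| Trial objectives | adherence |
| Outcome measures | six categories, no dichotomy |
| Sample size | no-show only |
| Statistical methods | five categories separately, plus an optional composite |

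The boundary of no-show is also loose. A woman who is silent, misses her slot and phones later that day fits both no-show and not attended-called. One who phones the day before, but less than 24 h ahead, fits no contact category.

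**3. What a no-show result says about attendance.** Assume that no-shows fall by the planned 7 points, that x of these points move to canceled/re-scheduled, and that the other categories do not change. The attendance gain is 7 − x. The range for x is assumed, because the article gives no cancellation rate. The power column is for no-show plus cancellation combined, at 924 per group and two-sided 0.05, with baseline cancellation assumed at 0 to 10%. It treats women as independent and makes no stepped wedge correction.

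| x (points) | Fall in no-shows | Gain in attendance | Power, combined outcome |
|---|---|---|---|
| 0 | 7 | 7 | 86–90% |
| 3.5 | 7 | 3.5 | 33–36% |
| 7 | 7 | 0 | 5% |

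Example for x = 3.5 with no baseline cancellation: rates 0.35 and 0.315. Power = Φ[(0.035 × √924 − 1.960 × 0.6662) / 0.6658] = Φ(−0.363) = 0.358.

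**4. Several routes to a claim.** If any one significant category counted as success, five tests at 0.05 would give 1 − 0.95⁵ = 0.226. Adding the composite gives 1 − 0.95⁶ = 0.265. Both assume independence, which is not exact because the categories compete for the same women. Whatever the dependence, the bound for five tests is 5 × 0.05 = 0.25. Splitting α instead would be costly: at α = 0.01 the no-show comparison has 74.7% power with 924 per group and would need 1308 per group for 90%.

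**The case against.** This is a condensed article without its analysis plan, and α allocation is commonly left to that plan. Blinding promises pre-specification and labels everything else exploratory, so an unseen plan could settle the endpoint. The Abstract's discussion, Sample size and Budget impact analysis all mention no-show, and the composite can be read as a sensitivity definition. A missing α rule is therefore not a fault in itself, and the optional composite is in tension with the pre-specification promise rather than in proven conflict with it. What stands is that the article itself gives differing versions of its primary outcome. The primary endpoint belongs in the protocol.

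A reader might go further, but the documents do not support these inferences:

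- **Cancellations are ignored.** They are a listed category of the primary outcome and may fall under the chi-square comparisons. They are missing only from the sentence on expected effects.
- **The reminder call will raise cancellations, or the whole 7-point fall could be relabelling.** No section says so, the timing of the call is not given, and the call is described as counselling women through barriers to attendance. Re-scheduled women may also be screened later.
- **All six categories are non-adherence.** Late-screened women are screened, and ineligible women are turned away for symptoms or incomplete paperwork.
- **Any significant category counts as trial success.** No section says this, so the error rate is conditional on such a claim being made.

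**Conclusion.** The point holds. The primary outcome is not fixed as one endpoint, and the sample size is for a narrower quantity than the adherence hypothesis. Under the assumed shifts of 0, 3.5 and 7 points, the same no-show result is compatible with an attendance gain of 7, 3.5 or 0 points at the booked appointment. This shows what the plan as written cannot distinguish through its powered comparison; it does not predict that the shift will happen. The family-wise error of about 23% is illustrative and applies only if one significant category out of five were presented as a positive primary result.

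**What to change.** Before intervention data are examined:

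1. Name one binary primary endpoint, tested at 0.05. Preferably this is screened at the booked appointment (on time or late-screened) versus not screened, because it matches the hypothesis.
2. State how every category is assigned, including attended on time, canceled/re-scheduled and ineligible, and close the overlap and the gap between the contact categories.
3. Use the same denominator of booked women in both periods, regardless of phone contact or consent. Ethical approval says "Verbal consent will be obtained for patients participating in the EBI reminder phone calls"; those calls belong to the intervention, so a denominator tied to them would not be comparable with baseline.
4. Make no-show the key secondary endpoint. Report all other categories, including canceled/re-scheduled, as secondary estimates without confirmatory claims.
5. Restate the planning rates and power for the chosen endpoint.

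If no-show is kept as primary, 924 per group stands as the uncorrected figure. The conclusion should then be limited to no-shows, with attendance and cancellation reported beside it.

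The cost is mainly wording. Data collection already provides for abstracting attendance from medical records, and Trial status reports that clinics are still collecting baseline measures. The downside is small: planning rates must be restated, and the stated power may become less favourable.
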